### Primary outcome

The primary outcome is the presence/absence of a clinically relevant change (improvement of at least 30%) in the visual analogue scale (VAS) score for pain at 6 months after baseline assessments (see Table 4). This choice is justified by the fact that it is relevant to the patient, figures in international recommendations [35–37], and is qualitative in nature. A qualitative outcome was also preferred because it should minimise the role of placebo effects, which are often significant for quantitative pain variables but not so for qualitative ones [38], and minimise effects associated with a lack of evaluator blinding, as is the case for self-evaluation questionnaires [39]. For the purposes of this study, a clinically relevant change in VAS scores for pain is defined by an improvement of at least 30% [40, 41]; improvements below this value will be considered as treatment failures (absence of clinically relevant change). Cases where patients demonstrate a 30% improvement in VAS scores for pain but nevertheless require hospitalization for back pain during the study follow-up period will also be considered as treatment failures.

**Table 4 Tab4:** Outcome measures

Patient-specific measure	Analysis metric and time frame	Planned analysis type
Number of patients with a clinically relevant change in visual analogue scale (VAS) score for pain, defined by an improvement of at least 30%; cases where patients demonstrate a 30% improvement in VAS scores for pain but nevertheless require hospitalization for back pain during the study follow-up period will be considered as treatment failures (absence of clinically relevant change)^a^	Proportion of patients with clinically relevant change for pain between baseline and 6 months	Comparison of distributions^b^
Huskinsson’s VAS for pain [25]. As recommended by national French health authority standards [26], this will address pain over the last 8 days	Repeated measures at baseline and 1, 6 and 12 months^b^	Mixed model for longitudinal data^c^
The Rolland & Morris (RMDQ) pain scale [27]: in this validated French version [28], a 24-question scale (with scores ranging from 0 (no impact) to 24 (maximum impact)) quantifies the impact of low back pain on daily life		
The Fear Avoidance and Belief Questionnaire (FABQ) assesses inappropriate fears and beliefs concerning back pain; the validated French version will be used [29]		
The EQ-5D-5L questionnaire [30, 31] will be used to track changes in quality of life. This self-administered questionnaire consists of two pages: the first contains the EQ-5D descriptive system and the second a visual analogue scale. The descriptive system has 5 dimensions (mobility, self-care, usual activities, pain/discomfort, anxiety/depression), each described by 5 levels of intensity (“no problems”, “slight problems”, “moderate problems”, “severe problems” and “extreme problems or complete inability”). The respondent must indicate one intensity level for each dimension	Repeated measures at baseline and 1, 6 and 12 months Proportion of patients with clinically relevant changes according to van der Roer et al. [32] at 1, 6 and 12 months	Mixed model for longitudinal data^c^ Comparison of distributions^b^
Patient Acceptable Symptom State (PASS): yes/no response to the following question: “If you take into account all the activities you have in your daily life, the importance of your pain and your disability, do you consider your condition as satisfactory?” [33]	Proportion of patients with patient-acceptable symptoms at baseline and 1, 6 and 12 months	Comparison of distributions^b^
Overall opinion of the patient on his/her state of health (5-point Likert scale)	Proportion of patients in each state at baseline and 1, 6 and 12 months	Comparison of distributions^b^
Overall opinion of the evaluating physician on the patient’s state of health (5-point Likert scale)		
Daily drug consumption over the past 72 h: • Analgesics (in milligrammes of paracetamol and morphine equivalents) • NSAIDs (reported in milligrammes and as a percentage of the maximum dose) [34] • Corticosteroids (in milligrammes equivalent prednisone) • Benzodiazepine muscle relaxants: % of maximum dose	Repeated measures at baseline and 1, 6 and 12 months	Mixed model for longitudinal data^c^
Number of infiltrations (epidural, posterior articular)	Centrality for the cumulative number of infiltrations at 12 months	Comparison of centrality^d^
Estimated per-patient cost for 1 year of care (based on observations of health resource use throughout the study: drug consumption, hospitalizations, imaging)	Centrality for the cumulative cost of care at 12 months	Comparison of centrality^d^

^a^ The primary outcome

^b^ The comparison of the number of patients improved (or other proportion) will be performed via distribution comparison tests for independent groups (either the uncorrected χ^2^ test, or Fisher’s exact test if the conditions for the χ^2^ test are not met)

^c^ A mixed model with patients as a random effect and study arm as a fixed effect will be used. A significant time × group interaction would indicate differences in the speed of recovery/change between groups

^d^ Means will be compared using the *t* test for independent groups when variable distributions are normal according to the Shapiro-Wilks test, or otherwise via the Mann Whitney test for comparing medians

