### Statistics

Statistical analyses will be performed by the Department of Medical Information at the University Hospitals of Montpellier, Montpellier, France, using the R programming environment [50] or SAS (enterprise guide V.7.1 or higher). An intention-to-treat structure will be implemented. The intention-to-treat population will include all randomised patients and will respect their allocations, regardless of whether or not they started the allocated interventions. Analyses may be adjusted according to clinical or inclusion criteria to take into account population heterogeneity. Though generally presented here, a more detailed statistical analysis plan will be drafted prior to the end of participant inclusion (and made available at https://osf.io/ahpwy/).

Descriptive statistics (for the total population and for each arm) will be provided as means with standard deviations for quantitative variables with normal distributions according to the Shapiro-Wilks test, or as medians with interquartile variables for other quantitative variables. Numbers and percentages will be provided for categorical variables.

As indicated in Table 4, the primary analysis is the comparison of the proportion of patients with a clinically relevant change in pain at 6 months; this will involve the uncorrected chi square (χ^2^) test for independent groups, or alternatively Fisher’s exact test if the conditions for the χ^2^ test are not met. We expect to perform an interim analysis of the number of patients in both groups with clinically relevant improvement as soon as there are 100 patients suitable for analysis with 6 months of follow up. The purpose of the latter is to assess futility, and a difference between arms (intervention – control) < 0 will stop the trial.

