As concerns secondary analyses, comparisons of qualitative variables will be performed in the same manner as for the primary analysis. The centrality of quantitative variables will be compared between arms using parametric (*t* test) or non-parametric (Mann Whitney test) analysis for independent groups, as appropriate. For longitudinal data, the preferred method will employ mixed models with patients set as a random effect and study arm as a fixed effect; an appropriate interaction term (group × time) will be used to detect differences between study arms in the rate of change. In addition, a medico-economic analysis comparing the two patient management strategies will be conducted according to international [51] and French recommendations [52]. A cost-utility analysis will be carried out, with utility values evaluated using the EQ-5D-5 L. The following direct medical costs will be considered: hospitalizations and consultations, transport, drugs and laboratory assessments.

Variables that are used for stratification (spa or presence of a professional activity) may be used in sub-group analyses. Covariate-interaction tests are the preferred method for detecting sub-group differences [53]. Statistical analyses will be adjusted on variables found to be imbalanced between arms. Sub-group tests will be considered as exploratory in nature.

The general hypothesis of the study supposes more improvement in the experimental arm as compared to the control arm. A difference will be considered statistically significant when the type I error rate is less than or equal to 0.05. As concerns missing data, patients lost to follow up will not be considered as withdrawn from the study but will be analysed as failures for the primary endpoint. Any deviations from the statistical analysis plan must be authorized by the study methodologist and will be thoroughly documented and justified in the study analysis report.

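### The secondary mixed models treat the pre-randomisation baseline as an outcome with a free arm effect, which costs precision that baseline adjustment would recover at no cost

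*Protocol article*

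**What the plan says.** Table 4 gives the time frame for VAS pain, RMDQ and FABQ as "Repeated measures at baseline and 1, 6 and 12 months", and gives the same time points for EQ-5D-5L and drug consumption. Footnote c sets the model: "A mixed model with patients as a random effect and study arm as a fixed effect will be used". It then names the test: "A significant time × group interaction would indicate differences in the speed of recovery/change between groups". The Statistics section repeats this, with "mixed models with patients set as a random effect and study arm as a fixed effect" and "an appropriate interaction term (group × time) will be used to detect differences between study arms in the rate of change". Table 3 and the section on allocation place the baseline assessments before randomisation.

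The PASS row of Table 4 reads "Proportion of patients with patient-acceptable symptoms at baseline and 1, 6 and 12 months". Footnote b says that such comparisons "will be performed via distribution comparison tests for independent groups", meaning an uncorrected chi-square or Fisher test.

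Two clauses in the Statistics section concern adjustment. One is permissive: "Analyses may be adjusted according to clinical or inclusion criteria to take into account population heterogeneity". The other commits to adjusting for variables that turn out to differ between the arms. The section also announces a more detailed SAP, to be drafted before inclusion closes.

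**The concern.** Baseline is measured before allocation, so the expected arm difference there is zero. A model that includes baseline in the outcome vector and gives arm its own effect at that visit estimates this known zero with error. It then subtracts the estimate from every later arm difference, which adds noise and gains nothing in validity.

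Disability and quality of life stand beside pain in the working hypothesis (Background). The sample size was set for the primary responder endpoint only, so no precision was budgeted for these outcomes. Wider intervals than the data allow could hide a real benefit on them.

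PASS is a smaller case of the same kind: its baseline answer is collected but the stated test at follow-up does not use it.

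**Working it through.** **The plan's own figure.** The only sample size is for the primary endpoint (40% versus 25%, alpha 4%, power 80%): 322, raised to 358 for 10% drop-out. Two-sided, the unpooled formula gives (2.054 + 0.842)² × (0.25×0.75 + 0.40×0.60) / 0.15² ≈ 159.3, so 160 per arm or 320. The pooled formula gives 326 and the arcsine formula 324. 322/0.9 = 357.8, so 358. The plan's figures reproduce and this point does not touch them. No power is stated for any secondary model.

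**Inputs for the check.** From the document: four visits (baseline, months 1, 6, 12), a patient random effect, arm, group × time, and 322/2 = 161 per arm. Assumed, because the document is silent: categorical time, complete data, correlation ρ between baseline and follow-up of 0.3, 0.5 or 0.7, equal SDs at first, two-sided 5%, and an illustrative effect of 0.30 SD.

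**Formulas, in units of SD² × 2/n.**
- As written (free arm effect at baseline): 2(1−ρ).
- Common baseline mean, or baseline as covariate: 1−ρ².
- Ratio, adjusted / as written: (1+ρ)/2.
- Follow-up value alone, ignoring baseline: 1.

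**Month-6 contrast, 161 per arm, effect 0.30 SD.**

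| ρ | As written | Adjusted | Ratio | Power as written | Power adjusted |
|---|---|---|---|---|---|
| 0.3 | 1.40 | 0.91 | 0.65 | 62% | 81% |
| 0.5 | 1.00 | 0.75 | 0.75 | 77% | 87% |
| 0.7 | 0.60 | 0.51 | 0.85 | 94% | 96% |

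For example, at ρ = 0.5 the standard error is √(1.00 × 2/161) = 0.1115 SD as written and √(0.75 × 2/161) = 0.0965 SD adjusted. Read as patients, the contrast as written needs 2/(1+ρ) times as many: 1.54, 1.33 and 1.18 times.

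A month-6 comparison that ignores baseline has 77% power for the same effect. The contrast as written is worse than that below ρ = 0.5, equal to it at 0.5 and better above it.

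**Unequal SDs.** Let k be the baseline SD divided by the follow-up SD. The variance as written relative to baseline as covariate is (k² + 1 − 2ρk)/(1−ρ²). At k = 0.7:
- ρ = 0.3: 1.07/0.91 = 1.18
- ρ = 0.5: 0.79/0.75 = 1.05
- ρ = 0.7: 0.51/0.51 = 1.00

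The loss disappears where ρ = k, because the regression slope of follow-up on baseline is then 1. The entry rule of 40 mm or more cuts off the lower part of the baseline VAS distribution, so a small k is plausible for VAS. No entry cut-off is set on RMDQ, FABQ or EQ-5D-5L.

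**PASS.** Adjustment for baseline PASS multiplies the variance by about 1−φ², where φ is the baseline to follow-up correlation (assumed). Borrowing 25% versus 40% for illustration, with 161 per arm and alpha 5%, power is 82.3% unadjusted, and 82.6%, 83.8% and 85.7% adjusted at φ = 0.1, 0.2 and 0.3. If few patients find their state acceptable at entry, φ is bounded: with 5% at baseline and 40% at follow-up it cannot exceed √(0.05×0.60/(0.40×0.95)) = 0.28.

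**The case against.** The strongest reply is that this is detail for the SAP. The article presents its statistics in general terms, calls mixed models the preferred method and does not even list a main effect of time. Not naming a baseline covariate is silence. This stands in part: the SAP is a natural place for the change. But the article does more than stay silent. It puts baseline in the outcome list and names the arm effect and the tested term, so a SAP that follows it literally inherits the inefficiency.

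Second, the references to speed and rate of change also fit a slope model with continuous time, and the figures above do not describe that test. This stands as a condition on the size. Nor does the Table 4 wording exclude other ways of handling baseline; the reading used here is the natural one, not the only one.

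Third, the adjustment clauses might be thought to cover the point. They do not cure it: one is optional, and the other depends on observed imbalance, whereas the gain comes from the correlation of baseline with outcome.

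Fourth, ρ, the SDs and the effect size are all assumed, and the loss can be nil. This also stands, and is why a range is given.

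**Conclusion.** The point holds as a loss of precision in secondary analyses. With categorical time and equal SDs, baseline adjustment cuts the variance of each arm-by-visit contrast to 0.65 to 0.85 of its value as written for assumed ρ of 0.3 to 0.7. With a narrower baseline SD, as is plausible for VAS, the gain is smaller and can vanish. For PASS it is about 0 to 3 power points for φ up to 0.3. The change is worth making because it costs nothing, not because the stated analysis is invalid.

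A reader might infer more, and the documents do not support it:
- **That baseline is wasted in the mixed models.** It is used, through within-patient change, but inefficiently. Above ρ = 0.5 the planned contrast beats ignoring baseline.
- **That the analysis is biased, or that the primary endpoint or sample size is affected.** Neither is so.
- **That a significance test of PASS at baseline is planned.** This is only an inference from the time points in the table; baseline could simply be described.
- **That fear-avoidance is part of the working hypothesis.** The Background names pain, disability and quality of life. FABQ is a secondary outcome analysed with the same model.

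**What to change.** In footnote c of Table 4, the Statistics section and the announced SAP, choose one of two forms:

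1. Keep baseline in the outcome vector but constrain both arms to a common baseline mean: no arm effect at baseline, with arm-by-visit terms at months 1, 6 and 12.
2. Use months 1, 6 and 12 as outcomes, with the baseline score as a covariate.

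State that visit is categorical, and report the adjusted arm difference with its confidence interval at each visit.

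For PASS at months 1, 6 and 12, use a logistic model with baseline PASS as a covariate and report a standardised risk difference. Present baseline PASS descriptively only.

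The cost is wording: no new data, visits or patients. The covariate form needs a rule for the occasional missing baseline score, such as single imputation; the constrained form avoids this.

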We propose to fill this methodological/knowledge gap by implementing a trial with the highest level of evidence possible. Our working hypothesis is that spa therapy in addition to usual care including home exercises (UCHE) will result in greater improvements in pain reduction, associated disability and quality of life in patients with chronic low back pain. It follows that health resource consumption and related costs should also be reduced. The primary objective of this study is therefore to compare the therapeutic effect of UCHE alone versus spa therapy in addition to UCHE for chronic low back pain (Fig. 1). Secondarily, we will also (1) evaluate the therapeutic effects specific to each spa centre, (2) specifically describe effects among subjects who are currently engaged in a professional activity, (3) evaluate treatment tolerance and (4) evaluate per-patient health resource use and associated costs.

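### The rule for 12-month cost and infiltrations will almost certainly end in a rank test, which addresses neither mean cost nor, in general, medians

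*Protocol article*

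**What the plan says.** Table 4 gives two outcomes the analysis type governed by footnote d. The metrics are "Centrality for the cumulative cost of care at 12 months" and "Centrality for the cumulative number of infiltrations at 12 months". Footnote d compares means by t test "when variable distributions are normal according to the Shapiro-Wilks test, or otherwise via the Mann Whitney test for comparing medians".

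The Statistics section repeats the choice in looser form: "The centrality of quantitative variables will be compared between arms using parametric" (t test) or non-parametric (Mann-Whitney) methods, as appropriate. The same section describes non-normal quantitative variables by median and interquartile values.

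The cost outcome in Table 4 is "based on observations of health resource use throughout the study: drug consumption, hospitalizations, imaging". Table 3, footnote h, adds sick-leave indemnities.

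Two other statements say what the cost result is for. The Background, after the working hypothesis on pain, disability and quality of life, says: "It follows that health resource consumption and related costs should also be reduced". It then lists per-patient resource use and costs as a secondary objective. The Statistics section says that "a medico-economic analysis comparing the two patient management strategies will be conducted", and adds: "A cost-utility analysis will be carried out, with utility values evaluated using the EQ-5D-5 L". It does not say how the cost difference in that analysis is estimated, and it does not alter footnote d for the Table 4 outcome.

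**The concern.** The footnote looks like a choice between two tests, but for these outcomes it is hardly a choice. Infiltrations are counts. Costs combine routine items with rare, expensive ones such as hospital stays. Neither will look normal at this sample size, so the t-test branch will practically never be used.

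The remaining branch is misdescribed and does not match the objective. Mann-Whitney asks whether a patient drawn from one arm tends to rank above a patient drawn from the other. Whether spa therapy lowers costs, and what it costs per unit of utility gained, depends on the mean, because total expenditure is the mean times the number of patients. Under the descriptive rule for non-normal variables, the Table 4 cost outcome, read as written, would be reported with neither a mean nor a test of means. At stake is whether this secondary outcome can answer the cost hypothesis, and whether it can be read alongside the cost-utility result.

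**Working it through.** **Arm size.** The plan gives no figure for the cost or infiltration comparison; its sample size is used here only to set the number per arm. The inputs are 40% versus 25%, type 1 risk 4% (taken as two-sided, which the plan does not state) and 80% power.

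- Pooled-variance formula, no continuity correction: 163 per arm, 326 in total.
- Unpooled variance: 160 per arm, 320 in total. The stated 322 lies between the two.
- Dropout: 322 / 0.90 = 357.8, so 358, or 179 per arm. Without inflation, 322 / 2 = 161 per arm.

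**Step 1: does the normality test ever pass?** Share of 1,000 simulated samples of 179 that Shapiro-Wilk rejects at 0.05:

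| Assumed distribution | Rejected |
|---|---|
| Lognormal, sigma 0.1 | 29% |
| Lognormal, sigma 0.2 | 79% |
| Lognormal, sigma 0.3 | 99% |
| Lognormal, sigma 0.5 and 1.0 | 100% |
| Poisson counts, mean 0.1 to 2 | 100% |

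Only nearly symmetric costs would reach the t test with any regularity.

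**Step 2: what does the fallback conclude about cost?** There were 1,500 simulated trials per setting; results are for 179 per arm at the 0.05 level. All cost values are assumptions in arbitrary units.

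- *Same shape, equal means* (lognormal sigma 1.0 in both arms): Mann-Whitney significant in 4.7%, Welch in 5.0%. No conflict.
- *Equal means, unequal skew* (sigma 1.2 control, 0.8 spa): Mann-Whitney significant in 95.2%, always towards higher spa cost; Welch in 4.9% + 1.3% = 6.2%. With 161 per arm, Mann-Whitney is at 92.0%. The rank test is not wrong about its own hypothesis, since the distributions do differ, but it says nothing about the equal means.
- *A charge of 200 to 500 for every spa patient, offset by fewer hospital stays* (10-15% control versus 2-5% spa, 6,000 to 8,000 each, on a lognormal base with mean 400): true mean cost is 160 to 440 lower with spa. Mann-Whitney is significant for higher spa cost in 99.8% to 100%. Welch is significant for lower spa cost in 13% to 59%, and for higher in at most 0.2%.

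**Step 3: what drives the reversal?** Take a simple two-value case: a hospital stay costs 6,000, with 12% of controls and 2% of spa patients hospitalised.

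- With a charge of 500 per spa patient: control mean 0.12 x 6,000 = 720; spa mean 0.98 x 500 + 0.02 x 6,500 = 620. Spa is 100 cheaper on average, yet P(spa > control) = 0.98 x 0.88 + 0.02 = 0.88.
- Without the charge: control mean 720; spa mean 0.02 x 6,000 = 120. P(control > spa) = 0.12 x 0.98 = 0.118; P(spa > control) = 0.02 x 0.88 = 0.018. Ranks and means agree.

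In this example the reversal comes from the cost common to all spa patients.

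**Step 4: infiltrations.** For Poisson counts with mean 0.1 to 0.5, the sample median was 0 in at least 99.7% of samples; at mean 1 it was not. Whenever fewer than half of the patients in each arm have an infiltration, both medians are 0 and comparing them is uninformative.

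**The case against.** A reader might infer that the planned test will declare spa therapy dearer when it is in fact cheaper. The documents do not support that. The reversal needs a charge borne by every spa patient, and the cost components named in Table 4, Table 3, the Secondary outcomes section and the Statistics section do not explicitly include the spa course. The hospitalisation rates and unit costs are also assumed. Unlike the two-value case, real controls continue previous treatment and would not cost zero. One could argue that the physical treatments in Table 3, or the transport item in the economic analysis, bring in a cost specific to the spa arm, but the text does not settle this.

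Nor can it be inferred that the cost-utility analysis is at fault. It is planned separately under international and French recommendations, nothing says that footnote d supplies its incremental cost, and it may well use a mean difference. Its estimation details can properly be left to a fuller plan.

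For infiltrations, Mann-Whitney handles ties and remains a valid test of equal distributions even when both medians are 0.

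These points limit the consequence but leave the core standing. Footnote d is a rule fixed in the current text, it will end in a rank test, and that test does not address the cost quantity that the plan wants to know. The unequal-skew setting needs no charge common to spa patients.

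**Conclusion.** The point holds as a mismatch between the stated test and the stated cost objective, and as a misdescription of Mann-Whitney. That the normality rule will fail is close to certain for any realistically skewed cost or count. Disagreement between ranks and means is a possibility: it requires the arms to differ in shape, and opposite directions additionally required an assumed cost common to all spa patients in the settings tried. The percentages above illustrate what can happen under assumed distributions and do not forecast this trial's result. If the cost-utility analysis does use means, the report could carry two cost results that answer different questions. For infiltrations the fault is confined to the reference to medians and the lack of an informative summary. The primary analysis and the sample size are unaffected.

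**What to change.** For 12-month cost, remove the Shapiro-Wilk condition and make the difference in arithmetic means with a bootstrap confidence interval the analysis (or a gamma model with log link), defined consistently with the cost-utility analysis. Any Mann-Whitney test should be labelled supplementary. A bootstrap is preferable to relying on Welch alone: under the most unequal skew tried (sigma 1.5 versus 0.8, equal means, 179 per arm), Welch rejected in 9.2% + 0.4% = 9.6% of trials.

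For infiltrations, delete the statement that the test compares medians and report the mean number per patient by arm, ideally with a rate ratio from a negative binomial or robust Poisson model. Mann-Whitney may stay as a test of equal distributions.

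Only analysis wording changes; no further data or patients are needed. The price is that the interval for mean cost may be wide, which reflects the precision the trial actually has.
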